## Abstract

**Background:**

Elevated stress can exacerbate cancer symptom severity, and after completion of primary cancer treatments, many individuals continue to have significant distress. Mindfulness-Based Cancer Recovery (MBCR) is an 8-week group psychosocial intervention consisting of training in mindfulness meditation and yoga designed to mitigate stress, pain, and chronic illness. Efficacy research shows face-to-face (F2F) MBCR programs have positive benefits for cancer patients; however barriers exist that impede participation in F2F groups. While online MBCR groups are available to the public, none have been evaluated. Primary objective: determine whether underserved patients are willing to participate in and complete an online MBCR program. Secondary objectives: determine whether online MBCR will mirror previous efficacy findings from F2F MBCR groups on patient-reported outcomes.

**Method/design:**

The study includes cancer patients in Alberta, exhibiting moderate distress, who do not have access to F2F MBCR. Participants will be randomized to either online MBCR, or waiting for the next available group. An anticipated sample size of 64 participants will complete measures online pre and post treatment or waiting period. Feasibility will be tracked through monitoring numbers eligible and participating through each stage of the protocol.

**Discussion:**

47 have completed/completing the intervention. Data suggest it is possible to conduct a randomized waitlist controlled trial of online MBCR to reach underserved cancer survivors.

**Trial registration:**

Clinical Trials.gov Identifier: NCT01476891

## Background

Receiving a diagnosis of cancer can be highly stressful, requiring psychological and behavioral adjustments to cope effectively with increased levels of stress that subsequently may affect psychological functioning [1] and cancer symptom severity [2]. The prevalence of clinical levels of distress in individuals with cancer is in the 35%–45% range [3-6]. Distress in these individuals most commonly presents as anxiety and mood disorders across stage and site of illness [3,7-9]. Therefore, the development and testing of accessible psychosocial interventions intended to reduce stress and improve mood and quality of life are important [10].

Interest in the potential health benefits of mindfulness meditation within the western medical system has increased with the development and proliferation of interventions modeled after the original Mindfulness-Based Stress Reduction (MBSR) program at the University of Massachusetts Medical Center, developed in the late 1970s by Jon Kabat-Zinn and colleagues [10,11]. Mindfulness meditation is the practice of cultivating moment-to-moment awareness of internal and external experience in an accepting and open manner [12]. MBSR is an 8-week group intervention consisting of intensive training in mindfulness meditation and Hatha yoga that is designed to treat symptoms of stress, pain and chronic illness [12]. Attitudes of open inquiry, patience, suspended judgment and compassion are encouraged and cultivated through the program during class and also through assigned daily homework. Individuals are taught to focus attention on sensations of the breath, body, and objects that enter awareness, such as thoughts and emotions, with the intention to fully experience the present moment [12]. One result of such focused attention in the present moment is reduction of rumination on the past or persistent worry about the future, as well as increased tolerance of uncomfortable emotional experiences (improved emotional regulation), which can result in decreases in symptomatology.

Research indicates F2F MBSR interventions are efficacious for treating a variety of symptoms associated with a range of chronic medical and psychiatric problems, including cancer [13-20]. Current literature, including the body of work from our research team on MBSR in oncology shows participation in F2F MBSR results in decreased stress symptoms, mood disturbance, anger, and fatigue, with concurrent increases in sleep quality, post-traumatic growth, spirituality and enhanced quality of life [14,21-29], as well as changes in several potentially important cancer biomarkers including immune function and stress hormones [30,31]. Several meta-analytic and comprehensive reviews of the effects of F2F MBSR in cancer concluded that it is a clinically valuable evidence-based intervention for cancer patients [16-18,20] with average Cohen’s *d* effect sizes for improving psychological and physical well-being of 0.48 and 0.18, respectively [20].

Despite their proven efficacy, there may be practical and psychological barriers to participation in F2F MBSR programs, such as geographic distance, cancer-related illness, fatigue, limited mobility or disability, child care, transportation, time, and self-consciousness, to name but a few. The Internet represents a promising method of delivering psychosocial interventions such as MBSR to underserved cancer patients who are unable to attend F2F programs. With the increase in Internet use and capabilities, psychosocial interventions are beginning to be offered online [32], and the use of synchronous online therapy that takes place in “real time” has increased. Fast broadband connection allows auditory and video exchanges that simulate the speed of F2F conversations, and videoconferencing using a broad range of software and programs is gaining greater use in therapy contexts [33,34]. In a meta-analysis, Barak et al., in 2008, compared the effectiveness of F2F psychological interventions such as Cognitive Behavioral Therapy (CBT) or Prolonged Exposure (PE) to Internet versions, and overall revealed comparable results [34]. Most similar to the proposed online MBSR study, Gardner-Nix and colleagues evaluated a non-randomized 10-week Mindfulness-Based Chronic Pain Management (MBCPM) intervention for chronic pain patients. The MBCPM program was based on the MBSR program, but additional emphasis was placed on learning to observe emotions associated with pain and general health education [35]. Patients received MBCPM via traditional F2F teaching, via videoconferencing at their local hospital, or were wait-listed. Baseline and post intervention measures showed patients in the F2F and videoconferencing groups achieved similar gains in mental health and pain catastrophizing relative to controls. However, the F2F group obtained significantly higher scores on the physical dimension of quality of life and lower pain intensity ratings than the videoconferencing group [35]. The authors concluded that while Internet interventions show potential for treating chronic pain patients, results may be better in person for some outcomes. While this study did use videoconferencing technology, advancements in sophisticated “real-time” technology since 2008 are significant and have potential to substantially enhance patient interaction and the overall patient experience. Our current study represents an advance over this methodology for several reasons: randomization of our participants, elimination of the need for patients to travel to treatment centres - increasing rural and remote individuals’ access despite geographic location, transportation issues, fatigue etc. We are also able to capitalize on the current technology for improved speed and quality of online communication in our trial.

The positive benefits of MBSR in individuals living with cancer have been well documented by our research team. However, practical and psychosocial barriers may impede participation and access to our popular F2F programs [34,36]. The Internet represents a promising method of delivering empirically supported psychosocial interventions such as MBSR to this underserved cancer population who are otherwise unable to participate, but it has never been evaluated in this context.

In this paper, we describe an ongoing trial to assess the efficacy of an online adaptation of an MBSR intervention for individuals diagnosed with cancer, online MBCR; the first of its kind. Participants are randomized to either an adapted online MBSR condition or a wait-list control condition. This study will help set the direction for future treatment studies to further evaluate online MBSR.

## Objectives

The eCALM Study’s primary objective is to determine feasibility – to examine whether moderately to highly distressed individuals diagnosed with cancer will be willing to participate in online 8-week MBSR groups and complete the intervention. This feasibility objective will objectively be assessed through evaluation of recruitment, retention, attendance, adherence and participant satisfaction. The secondary objective is to examine the efficacy of the online synchronous adaptation of an MBSR intervention for individuals diagnosed with cancer compared to a treatment-as-usual (TAU) wait-list group on a range of previously studied patient-reported outcomes (PROs) including mood, symptoms of stress, post-traumatic growth, spirituality and mindfulness.

### Hypotheses

**1)** Participants will be willing to participate and complete an 8-week online MBSR intervention. Our estimated feasibility outcome proportions of 5% interested, 30% eligible, 85% consent, and 85% complete the intervention will be deemed feasible if within 5% of each target; **2)** Participants in the online MBSR treatment condition will demonstrate greater decreases in symptoms of stress and mood disturbance over the course of the intervention, when compared to participants in the wait-list control condition; **3)** Participants in the online MBSR condition will demonstrate greater increases in mindfulness, spirituality and posttraumatic growth over the course of the intervention, when compared to participants in the wait-list condition.

## Methods

### Study design

Figure 1 illustrates the overall study design and participant flow for the trial. This study utilizes a randomized wait-list controlled trial design with pre- and post-assessment. Ethics approval was obtained from the University of Calgary, Conjoint Health Research Ethics Board (CHREB). While the wait-list trial design may limit potential long-term follow-up, preventing conclusions about efficacy of the treatment to maintain effects after this specified time frame, recruitment with a no-treatment control may compromise our ability to accrue participants. Additionally, a wait-list design can control for the influences of pre- and post-treatment assessment, symptom self-monitoring, natural recovery from cancer treatments and spontaneous remission or deterioration of symptoms.

**Figure 1 F1:**
[figure not shown]
Overall trial design and participant flow diagram.

### Eligibility

Inclusion criteria: 1) Age 18 years or older; 2) Speak and read English sufficiently to complete questionnaires; 3) Women and men who have been diagnosed with of any type of cancer, at any time in the past with no restriction on tumour site; 4) Before or currently receiving primary treatment, or completed primary treatment within the last 36 months. This time was chosen in order to assure a group of individuals who were fairly recently involved in diagnosis and treatment, thus also increasing the likelihood that the issues they are dealing with will be more similar, but also including individuals up to 3 years post primary cancer treatment who still feel significant distress; 5) Exhibiting moderate distress as established by responses on the Distress Thermometer (DT) of 4 or greater out of 10. This is an important criterion as statistical problems with floor effects are common in volunteer samples who have relatively high levels of functioning prior to trial involvement; 6) Willing to participate in the intervention requirements; able to participate in the intervention (2 hours per week for 8 weeks, and the full-day retreat), and agree to the randomization procedure; 7) Internet access; self-reported familiarity with computer usage and Internet access with an overall point 5 Megabyte capability and minimum download (2 Megabytes) and upload (500 Kilobytes) is necessary; and 8) Residents in Alberta, who have limited access to existing F2F MBSR programs.

Exclusion criteria: 1) Concurrent self-reported diagnosis of psychosis, bipolar disorder, substance abuse or suicidality. Individuals with depression, anxiety or adjustment disorders are not excluded; 2) Individuals who have previously participated in an F2F MBSR group.

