### Recruitment

Potentially eligible participants in Alberta are identified through media outreach, promotional pamphlets, community based networks, and by cancer registry case records to mail study invitation letters. In Alberta, only one major cancer centre has MBSR classes specifically for individuals diagnosed with cancer; therefore all individuals who are unable to attend these F2F classes would be eligible to participate. The Alberta Cancer Registry estimates as of September 2011, 25,000 individuals diagnosed with cancer are eligible to be contacted for the trial. According to research conducted by the PI, approximately 35-45% of these individuals will meet criteria of being distressed. Additionally, 77% of Albertans 16 years of age and older have Internet access and 429 communities throughout the province of Alberta have broadband Internet (http://www.albertacanada.com; http://www.albertasupernet.ca). This forms a potentially large cohort to identify individuals living with cancer who have Internet access for this study.

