### Outcome measures and questionnaires

Table 1 contains the outcome measures and their administration timing for the online MBCR and wait-list group participants. Medical history (i.e., type of cancer, dates of diagnosis and treatment, and types of treatment received) and demographic information (i.e., sex, age, ethnic background, education, marital status, and current employment status) is obtained at the first assessment and later verified in the participant’s medical chart, with consent. Participants are also asked to indicate how much experience with meditation and/or yoga they have had previously.

**Table 1 T1:** Outcome measures for the online mbcr and wait-list group participants

***Construct***	***Measure***	***Administration***
Primary Objective: Feasibility	See Figure 1 for estimates –study deemed feasible if within 5% of each target value	
Program Satisfaction	eCALM –Online MBCR Program Evaluation Form	· Post intervention only
Dose of intervention delivered and dose received	Delivered: Attendance log Received: Meditation Log	· Throughout intervention
Distress Screening	Score of 4 or higher on the Distress Thermometer (DT)	· Pre intervention only
Primary Measure of Secondary Objective: Mood	Profile of Mood States (POMS)	· Pre and Post MBCR or wait
Other Secondary Outcomes: Stress	Calgary Symptoms of Stress Inventory (C-SOSI)	· Pre and Post MBCR or wait
Post-Traumatic Growth	Post-Traumatic Growth Inventory-Revised (PTGI-R)	· Pre and Post MBCR or wait
Mindfulness	Five Facet Mindfulness Questionnaire (FFMQ)	· Pre and Post MBCR or wait
Spiritualty	Functional Assessment of Chronic Illness Therapy-Spiritual Well-Being (FACIT-sp)	· Pre and Post MBCR or wait

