### Analytic strategy

#### Analysis of power for primary effects

The target sample size for this study was based on achieving adequate power for the secondary analyses (since the primary analyses were proportions based on feasibility). The goal was to have 80% power at a significance level of .05, to test the efficacy of the online MBCR intervention in reducing mood disturbance, compared to the control group. On the basis of observed means and standard deviations in three F2F comparable trials [22,26,46]: the estimated effect sizes for group differences in pre- to post-intervention change on the POMS total mood disturbance score was 0.72, 0.51 and 0.58 respectively. Based on the three trials above, and following the more conservative estimation rule proposed by Dattalo (2008) [47] to use t-test estimations for RM-ANOVA designed studies, 26 participants are required for each group to detect a significant difference between the groups. Taking into account the likelihood of 20% attrition as observed in F2F MBSR trials, a total of 32 participants will be recruited for each group—a total sample size of 64 participants.

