### Data analysis

All data analysis will be carried out at the completion of the study using the most up-to-date version of SPSS for Windows. Tests will be performed with a two-sided alternative hypothesis, at a critical significance level of 5%. To ensure the appropriateness of the analysis the distributional normality of the data will be confirmed. Wherever possible, p-values and effects sizes will be reported.

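### The prior-training exclusion names only face-to-face MBSR, so people already trained in online MBCR, the format under test, can be randomised to either arm

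*Protocol article*

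**What the plan says.** The Eligibility section of the protocol article has two exclusion criteria. The first concerns self-reported psychiatric conditions. The second is the only one about earlier training, and it covers "Individuals who have previously participated in an F2F MBSR group".

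Three other places bear on it:

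- **Abstract, Background:** "While online MBCR groups are available to the public, none have been evaluated".
- **Recruitment:** one major cancer centre in the province runs face-to-face classes, "therefore all individuals who are unable to attend these F2F classes would be eligible to participate". No limit on earlier online training is stated there.
- **Outcome measures and questionnaires:** "Participants are also asked to indicate how much experience with meditation and/or yoga they have had previously". The answer is baseline information. The article gives it no role in eligibility or in the analysis.

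The POMS total mood disturbance score is analysed by a 2 (group) × 2 (time) repeated-measures ANOVA, and the other patient-reported outcomes in the same way. Feasibility, the primary objective, is judged on four proportions: interested, eligible, consented and completed. Each is to lie within 5% of its target, and the completion target is 85%.

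**The concern.** The article does not explain the second exclusion. Its evident purpose is to keep out people who have already had the programme, but it does so for one delivery format only. The format left out is the one being tested, and the article itself says the public can obtain it. The trial also requires Internet access and limited access to face-to-face programmes, so for an entrant with earlier training an online course is a plausible source.

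Two results could be affected. If previously trained people gain less from repeating the programme, the difference in change between the arms shrinks. And if some entrants have already taken the online format, the consent and completion proportions say less about willingness among people new to it, which is what a feasibility study of a new delivery format is meant to show.

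**Working it through.** **1. The text.** Take a person who has completed a public online MBCR course, has never attended a face-to-face group, and meets the eight inclusion criteria. Neither exclusion applies, so the person is eligible and can be allocated to either arm. Replace the online course with a face-to-face one and the person is excluded. The point rests on this comparison; the arithmetic below only indicates scale.

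**2. The planning figures.** The power section states effect sizes for the group difference in POMS change: the estimate "was 0.72, 0.51 and 0.58 respectively". Their mean is (0.72 + 0.51 + 0.58) / 3 = 0.603. It aims for "80% power at a significance level of .05" and concludes that "26 participants are required for each group to detect a significant difference between the groups". A two-sided, two-sample t-test at 5% and 80% power needs 32 per group at 0.72, 48 at 0.58, 62 at 0.51 and 45 at 0.603, so 26 is not reproduced from the stated inputs. That is a separate matter. Here it means only that the starting level of power in the table is already below 80%, and the table should be read down its columns for the change.

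**3. Dilution, as illustration.** Let q be the share of participants already trained. The documents do not give q, so the range 0 to 20% is an assumption. Suppose also that these people show no between-arm difference at all. Then

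effective d = d × (1 − q).

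With 26 analysed per group, two-sided 5% t-test:

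| q | effective d (from 0.603) | power | n per group for 80% power |
|---|---|---|---|
| 0 | 0.603 | 57% | 45 |
| 2% | 0.591 | 55% | 46 |
| 5% | 0.573 | 53% | 49 |
| 10% | 0.543 | 48% | 55 |
| 20% | 0.482 | 40% | 69 |

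The no-further-gain assumption is severe. If trained entrants kept half the benefit, the factor would be (1 − q/2), and q = 10% would have the effect shown in the 5% row: 0.603 × 0.95 = 0.573.

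**4. Completion, as illustration.** Assume that newcomers complete at 80% and previously trained entrants at 100%. The observed rate is 0.80 × (1 − q) + q, which gives 80.4% at q = 2%, 81% at 5%, 82% at 10% and 84% at 20%.

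Reading the margin as 5 percentage points, the lower limit is 85 − 5 = 80%. If newcomers completed at 78%, the share needed to lift the total to 80% solves 78(1 − q) + 100q = 80, so q = 2/22 = 9.1%. A small share would change the verdict only when the newcomers' rate is already close to the limit.

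**5. Evidence on q.** The Discussion itemises the ineligible responders: 8 + 3 + 12 + 9 + 6 + 2 + 1 = 41. None is listed as excluded for earlier MBSR. Only the face-to-face format was an exclusion, so this does not measure online exposure, but nothing in the article points to a large share.

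**6. Reach of a rewording.** 57 of the planned 64 were enrolled at the time of writing, which leaves 64 − 57 = 7.

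**The case against.** The strongest reply is that the gap is real on paper and immaterial in practice. The article describes the population as underserved, public availability is not evidence of uptake, and no responder is recorded as excluded for earlier MBSR. Most of this stands, and it is why the share is taken to be small. The last argument is weaker than it looks: the trial recruits people with limited access to face-to-face classes, so few exclusions on that ground would be expected whatever their online experience.

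A reader might infer more than the documents support in five ways:

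- **Bias between arms.** Not supported. Randomisation balances earlier training on average, so the expected effect is dilution.
- **Earlier training acting as treatment in the wait-list arm.** Not supported. The analysis concerns change from T1 to T2, and training finished before T1 is already in the baseline score. Only a course taken during the wait could act in that way. The comparator is usual care while waiting, with which outside resources are arguably compatible, and wait-list members are told their start date.
- **No provision at T2 for recording outside courses.** Not supported. The article says the T1 and T2 batteries are identical, but it condenses a fuller protocol and does not show every item.
- **No further gain in trained entrants.** An assumption. Every entrant must score at least 4 on the Distress Thermometer, so a trained entrant still has distress that could fall.
- **Feasibility certainly inflated.** Plausible, but assumed. Someone who has finished one course might be less willing to commit to another eight weeks and a retreat.

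It could also be said that the baseline question on meditation and yoga already covers the matter. It helps to describe prior practice by arm, but as described it asks how much experience a person has and need not identify an MBSR or MBCR course.

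**Conclusion.** The stated exclusion admits people already trained in the format under test while barring those trained in the other format, and the article gives no reason. That much follows from the text alone.

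The consequence is modest and unquantified: possible dilution of the efficacy contrast, and feasibility proportions that may partly describe people who are not new to online MBCR. At a share of 2% the loss of power at d = 0.603 is about two percentage points (57% to 55%). The larger losses at 10% and 20% are illustrations, not estimates. All these figures depend on an assumed share and on no further gain among the previously trained. The completion figures depend on assumed rates in both groups. This is a cheap clarification worth making, not a threat to the validity of the comparison.

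**What to change.** For remaining entrants, reword the second exclusion to cover previous participation in any MBSR/MBCR programme, face-to-face or online. On the figures in the Discussion this reaches about seven people.

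For those already enrolled, ask one direct question: has the participant taken an MBSR or MBCR course before entering the trial, in any format? The existing meditation and yoga item should not be relied on for this. Then report the feasibility proportions and the POMS effect with and without those who answer yes, as a sensitivity analysis. Completion can be recomputed directly, because its denominator is those who consented. The consent and eligibility proportions can be recomputed only approximately unless callers who did not enrol were also asked, and the report should say so.

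The cost is a few otherwise eligible callers, one extra question and one short table. If nobody answers yes, the table shows that the issue did not arise among those enrolled.
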